## Abstract

**Background:**

Diabetic retinopathy (DR) and age-related macular degeneration (AMD) are 2 of the leading causes of vision loss worldwide. As population aging and diabetes prevalence increase, timely detection of these conditions has become essential. However, limited professionalism and insufficient training in ophthalmic screening among general medicine physicians may lead to delayed diagnosis and treatment. Artificial intelligence (AI)–assisted diagnostic tools may help to improve the screening of DR and AMD in routine clinical practice.

**Objective:**

This study aims to evaluate the clinical effectiveness and cost-effectiveness of AI-assisted fundus imaging for DR and AMD screening in adults with diabetes and older adults at risk of macular degeneration.

**Methods:**

This multicenter, 2-arm, parallel-group, open-label, individual-level randomized controlled trial and patient recruitment are performed at the settings of Family Medicine and Geriatric and Gerontology Care over 4 medical centers in Taiwan. Eligibility includes (1) diabetic individuals aged ≥20 years for DR screening, and (2) individuals aged ≥50 years for AMD screening. The study protocol has been approved by the ethics committees of all participating hospitals, and all participants will provide written informed consent.

**Results:**

The study was funded in September 2024, began on October 2, 2025, and is expected to be completed in December 2027. After the pilot implementation phase without randomization, participants will be randomized 1:1 into two groups: (1) AI-assisted screening, and (2) usual physician-only screening. The primary outcomes will include the detection rates (defined as participants with confirmed DR or AMD among all screened participants) and the positive predictive values (defined as participants with confirmed DR or AMD among those who tested positive). Cost-effectiveness analyses will be performed using data derived from the trial results.

**Conclusions:**

This study will provide robust evidence on the effectiveness of AI-assisted ophthalmic screening in improving patient eye health outcomes through timely screening and accurate early detection. This strategy may be cost-effective.

## Introduction

Diabetic retinopathy (DR) is one of the most common retinal vascular diseases and a microvascular complication of diabetes, affecting approximately one-third of patients with diabetes [1]. It primarily impacts the retinal microvasculature and leads to retinal hemorrhages, microaneurysms, lipid exudates, and, in severe cases, neovascularization [2]. DR is a leading cause of vision impairment and blindness [3]. As the global aging population increases, the number of older individuals with diabetes continues to grow, contributing to a rising prevalence of DR [4,5]. Age-related macular degeneration (AMD), which affects the macula in individuals aged >50 years and is a leading cause of irreversible blindness, has an overall prevalence rate of 8.69% [6]. Early-stage AMD features drusen and abnormalities of the retinal pigment epithelium, while late-stage AMD is classified into 2 forms: neovascular (wet or exudative) and nonneovascular (dry, nonexudative, or atrophic) [2,3].

Effective screening and prompt intervention are crucial for preventing permanent vision loss. However, patients with diabetes and older people often have limited awareness of DR and AMD, poor compliance with fundus checks, and delayed seeking medical help. As chronic disease management mainly takes place in general medicine clinics, where physicians might find interpreting retinal images challenging, timely referrals to ophthalmologists are crucial. Introducing a reliable screening tool in general medicine settings can increase access to fundus examinations, enhance early diagnosis, and improve treatment outcomes.

In recent years, artificial intelligence (AI) technology has led to the development of deep learning software apps for medical image recognition and analysis, providing diagnostic support to general frontline physicians [4]. AI has demonstrated accurate performance in analyzing images from the fundus photography [5-7]. Using AI-based detection, classification, and algorithms [8], these tools offer high diagnostic accuracy for diseases such as AMD [9,10], DR [11], and glaucoma [12]. To address the high demand for specialist expertise and manpower, AI-assisted diagnostic software based on fundus photography in Taiwan, such as VeriSee AMD and VeriSee DR (Acer Inc), has been shown to enable physicians to rapidly identify retinal diseases [13-15]. However, whether AI-assisted screening can outperform traditional physician-led screening in real-world settings, particularly in terms of patient outcomes, remains unclear [16]. Furthermore, whether this technology can improve cost-effectiveness by reducing medical expenditures and improving patients’ quality of life through early detection and treatment is a critical issue that must be established from a health insurance reimbursement perspective. To date, limited evidence from pragmatic randomized trials [17] has examined the integration of AI-assisted retinal screening into routine general medicine workflows, particularly with simultaneous evaluation of clinical effectiveness, referral patterns, and economic outcomes [7]. In addition, existing evidence has largely focused on DR, with comparatively less attention given to AMD [18,19]. Addressing these gaps is essential for informing real-world implementation and reimbursement decisions.

The aim of this study is to evaluate the effectiveness and cost-effectiveness of integrating AI-assisted retinal screening tools for DR and AMD into routine clinical practice through a pragmatic randomized controlled trial (RCT) embedded in routine clinical care. The hypothesis is that incorporating AI-assisted retinal screening into routine care may facilitate earlier disease detection, improve patient outcomes, and represent a cost-effective strategy, thereby providing robust evidence to support the real-world adoption of AI technologies across diverse clinical settings.

## Methods

### Study Design

This study adopts a 2-phase design. The first phase is a pilot feasibility study conducted to evaluate system integration, workflow functionality, and operational readiness of AI-assisted retinal screening within routine clinical practice. The pilot phase began on October 2, 2025, and is expected to last for approximately 6 months to 1 year.

The decision to proceed to the second phase will be guided by referral rate–based criteria, based on pragmatic randomized trials [20,21], and progression to the second phase is not guaranteed.

The second phase is a multicenter, 2-arm, parallel-group, open-label pragmatic randomized clinical trial designed to evaluate the effectiveness of AI-assisted retinal screening compared with conventional physician-based screening. Owing to the nature of the intervention, blinding of the physicians performing the screening assessments is not possible. In addition, the ophthalmologists conducting the confirmatory diagnostic evaluations will not be blinded to group allocation, as the presence or absence of an AI-generated report may allow them to infer the assigned screening strategy. It reflects the real-world practice of using this AI instrument. Cost-effectiveness analyses will be conducted using trial data to simulate long-term economic benefits. The flowchart of this study is shown in Figure 1. The study followed the SPIRIT (Standard Protocol Items: Recommendations for Interventional Trials; Checklist 1) for RCT guideline [22].

**Figure 1. F1:**
[figure not shown]
Illustration of study design. This figure illustrates the overall study design, including participant enrollment, informed consent, randomization to the artificial intelligence (AI)–assisted screening group or the conventional physician-based screening group, screening procedures, ophthalmology referral pathways, and follow-up for outcome assessment. AMD: age-related macular degeneration; DR: diabetic retinopathy; NTUH: National Taiwan University Hospital; RCT: randomized controlled trial.

### Study Settings

To ensure the performance of the AI screening test, a diagnostic accuracy study will be conducted concurrently with the RCT in the ophthalmology setting. Patients who visit the ophthalmology outpatient department will be invited to undergo the AI screening test without randomization, followed by confirmation of the diagnosis by the ophthalmology specialists. The reference standard will be diagnoses made by ophthalmologists. As both screen-positive and screen-negative individuals will undergo confirmatory assessment, sensitivity, specificity, and overall accuracy can be evaluated, which differs from the outcome assessment used in the randomized clinical trial (registration NCT06843499).

In the clinical trial, the study population will consist of adult patients attending family medicine and geriatric and gerontology outpatient clinics at the National Taiwan University Hospital (NTUH) Main Branch and Bei-Hu Branch, Fu Jen Catholic University Hospital, and Min-Sheng General Hospital in Taiwan.

### Inclusion and Exclusion Criteria

Inclusion criteria include adults aged ≥20 years with diabetes undergoing screening for DR and adults aged ≥50 years undergoing screening for AMD. Potential participants will be identified during routine clinic visits, and eligible individuals who express interest will receive detailed study information. Written informed consent will be obtained prior to enrollment. Participants will be excluded if they decline participation or are unable to provide informed consent because of cognitive or communication limitations.

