### AI Platform Functionality

AI-assisted retinal screening will be operationalized through the AI Imaging Management, Integration, and Governance System (AIMIGS), a centralized platform designed to govern, integrate, and deploy medical imaging–based AI models within routine clinical workflows (Figure 2). Within this trial, AIMIGS automatically routes eligible fundus photographs from the hospital Picture Archiving and Communication System (PACS) to the designated AI screening models (VeriSee DR and VeriSee AMD) according to predefined rules based on imaging modality, clinical order information, and participant allocation. AI-generated outputs, including image quality assessment, disease suspicion, and screening parameters, will be collected and returned to the AI PACS server and report information system, where they will be made available to treating physicians during clinical encounters. Clinicians are provided with AI-assisted outputs integrated into the clinical workflow. These include referral recommendations (positive or negative), disease severity grading for DR and AMD, image quality assessment, and lesion-level annotations where applicable. The AI results are presented through the electronic health record (EHR) system to support clinical decision-making. The AI system evaluates fundus images based on predefined technical criteria (eg, clarity, illumination, and visibility of key retinal structures), and images not meeting these criteria will be flagged as insufficient quality (Figure 3). Physicians may also independently identify images as inadequate for clinical interpretation. In such cases, repeat imaging will be performed. AIMIGS incorporates a rule engine module that enables automated and protocol-compliant random assignments.

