### Randomization

Participants will be randomized at the individual level in a 1:1 ratio to either the AI-assisted screening group or the conventional physician-based screening group. Randomization is performed on a per-participant basis, and sample size estimation will be based on this process. DR and AMD are managed within a single unified cohort. DR and AMD can be diagnosed in the same patient, while DR and AMD are treated as separate disease-specific outcomes, and analyses will be conducted independently for each condition based on predefined eligibility criteria. Participants eligible for both conditions may contribute to both analyses.

In the conventional physician-based screening arm, fundus photographs will be interpreted by physicians without the use of any AI assistance. Physicians will review the images independently based on their clinical judgment. All physicians involved in image interpretation will receive standardized training in fundus photograph assessment prior to study initiation. In addition, a standardized reading guide will be provided to ensure consistency in image interpretation across the control group.

Randomization will be conducted using a computerized randomization module embedded within the rule engine of AIMIGS. After enrollment, each participant will be assigned a unique study ID, and allocation will be automatically generated by AIMIGS. Once the assignment is generated, the system automatically allocates each participant to the designated study arm and triggers the corresponding imaging procedures according to the predefined workflow.

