### Referral After a Positive Test

The examination will be repeated for images that are of insufficient quality for clinical interpretation. Across both groups, ophthalmology referral will be provided for participants with DR of stages 2 to 4 or AMD of stages 3 to 4, whereas participants not meeting these severity thresholds will be advised to undergo regular annual follow-up examinations. Confirmatory diagnosis of DR and AMD will follow the Early Treatment Diabetic Retinopathy Study [16], AREDS scales [23], and Beckman Initiative Classification [23] (Textbox 1). At 8 weeks after screening, referral completion and diagnostic outcomes will be assessed through review of electronic medical records, hospital visit records, and, when necessary, telephone follow-up.

Textbox 1.Confirmatory diagnosis of diabetic retinopathy (DR) and age-related macular degeneration (AMD).Diabetic retinopathyAccording to the Early Treatment Diabetic Retinopathy Study severity scale [24], primarily diagnosed through fundus photography and indirect ophthalmoscopy to identify typical features such as microaneurysms, retinal hemorrhages, hard exudates, and cotton-wool spots (soft exudates).Fluorescein angiography is generally not used as a primary diagnostic tool; however, it may be used in the evaluation of macular ischemia, edema, or neovascularization to inform treatment strategies. It facilitates the verification of the location and extent of lesions.The severity of DR is categorized into 5 stages: no diabetic retinopathy (no DR, stage 0), mild nonproliferative diabetic retinopathy (NPDR; stage 1), moderate NPDR (stage 2), severe NPDR (stage 3), and proliferative diabetic retinopathy (PDR; stage 4).Age-related macular degeneration:According to the Age-Related Eye Disease Study severity scale [25], fundus photography and indirect ophthalmoscopy are primarily used to identify the location, size, and number of drusen.On the basis of the Beckman Initiative Classification [23], AMD is classified into 4 severity levels based on drusen size and pigmentary abnormalities: no AMD (stage 1), early AMD (stage 2), intermediate AMD (stage 3), and advanced AMD (stage 4).When necessary, fluorescein angiography and optical coherence tomography are used to detect the choroidal neovascularization associated with AMD, the presence of macular edema, and retinal pigment epithelium abnormalities.

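### People already read by the AI in the unrandomised pilot stay eligible for the randomised phase, so some controls may carry an earlier AI report and the detection difference would shrink in proportion to the overlap

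*Protocol article*

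**What the plan says.** All references are to the Protocol article.

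- **Inclusion and Exclusion Criteria.** Entry needs diabetes and age 20 or over (DR), or age 50 or over (AMD). The exclusions are: "Participants will be excluded if they decline participation or are unable to provide informed consent because of cognitive or communication limitations".
- **Abstract, Results.** The order of the phases is clear: "After the pilot implementation phase without randomization, participants will be randomized 1:1 into two groups".
- **Study Design.** The pilot is to test, among other things, "operational readiness of AI-assisted retinal screening within routine clinical practice". Its timing: "The pilot phase began on October 2, 2025, and is expected to last for approximately 6 months to 1 year".
- **Referral After a Positive Test.** For people below the referral thresholds: "participants not meeting these severity thresholds will be advised to undergo regular annual follow-up examinations".
- **AI Platform Functionality.** On where the output goes: "The AI results are presented through the electronic health record (EHR) system to support clinical decision-making". The text accompanying Figure 3 adds that AI reports can be integrated into the record as clinical documentation.
- **Randomization.** In the control arm, "fundus photographs will be interpreted by physicians without the use of any AI assistance". The Intervention section adds that control referral rests only on the physician's own judgment.
- **Study Settings.** A separate accuracy study runs alongside the trial: "Patients who visit the ophthalmology outpatient department will be invited to undergo the AI screening test without randomization".
- **Statistical Analysis.** Earlier AI exposure appears in neither the listed subgroups nor the listed covariates.

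**The concern.** The trial compares a physician with AI output against a physician without it. That contrast needs controls whose physician has no AI reading of their retina. A pilot participant who returns for a yearly check meets the age and diabetes criteria again and is caught by neither exclusion. If allocated to control, the new photograph is withheld from the AI, but the earlier AI grade may already be in the record the physician opens.

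The contrast can weaken in two ways. The control physician may act on the earlier report. Also, disease the AI could find may already have been found in the pilot, leaving less for either arm to detect. Both push the detection difference towards zero in a trial designed to show superiority. Without a record of who was exposed, the analysis could not separate these people out.

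**Working it through.** **Step 1. Does the timetable allow overlap?** The pilot starts on 2 October 2025 and lasts 6 to 12 months, so it ends between about April and October 2026. Yearly returns then begin in October 2026, and the last fall between about April and October 2027. The study is expected to finish in December 2027, so the returns fall within the period left for the randomised phase. This assumes that the pilot uses the trial's clinics and that its participants receive the same annual advice; the document states that advice for the two trial groups. It also assumes that the second phase goes ahead, which the document does not guarantee.

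**Step 2. Does any rule stop it?** The exclusions do not. The control-arm rules govern the image being read. No passage masks or handles an AI report already on file.

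**Step 3. Reproduce the planned sample size.** Inputs from Sample Size Estimation: DR 10% against 15%, AMD 5% against 10%, two-sided alpha 0.05, power 90%, referral completion 70%. The formula is

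n per arm = (1.960 + 1.282)² × [p₁(1−p₁) + p₂(1−p₂)] / (p₂−p₁)² ÷ 0.70

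- DR: 10.507 × (0.0900 + 0.1275) / 0.0025 = 914.1; ÷ 0.70 = 1305.9 (stated 1306).
- AMD: 10.507 × (0.0475 + 0.0900) / 0.0025 = 577.9; ÷ 0.70 = 825.6 (stated 825).

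The stated sizes reproduce. They make no allowance for AI exposure among controls.

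**Step 4. Illustrate the dilution (DR).** The intention-to-screen detection rate counts unreferred positives as not detected. The rates are therefore 0.70 × 10% = 7.0% and 0.70 × 15% = 10.5%, with 1306 per arm. Let f be the share of participants AI-read before, and r their detection rate, assumed equal in both arms:

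rate in each arm = (1−f) × p + f × r, so the difference = (1−f) × 3.5 points

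Both f and r are assumptions. I take r = 2% (most disease already found) or r = 7% (same as an ordinary control). Power is from the two-proportion normal approximation.

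| f | Difference, points | Power, r = 2% | Power, r = 7% |
|---|---|---|---|
| 0 | 3.50 | 88.6% | 88.6% |
| 10% | 3.15 | 84.0% | 82.0% |
| 20% | 2.80 | 78.1% | 73.2% |
| 30% | 2.45 | 70.6% | 62.5% |

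**Step 5. Check with a different mechanism.** Suppose instead that exposed controls behave exactly like the AI arm: control rate = 10% + f × 5 points, with an effective 0.70 × 1306 = 914 per arm. DR power is 90% at f = 0, 86% at 5%, 82% at 10%, 72% at 20% and 60% at 30%. AMD, with 0.70 × 825 = 577.5 per arm, gives 90%, 86%, 82%, 71% and 58%. The two models agree on direction and rough size.

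**The case against.** **A condensed article may leave this to the full protocol.** An ethics-approved version exists and is not shown, and it may carry the rule. But the article prints its exclusions explicitly, and as printed they admit these people. The point stands, and quoting an existing rule would close it.

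**The size has no documentary basis.** This is right. A reader might infer a large effect by applying the planned 870 DR enrolments a year to a 6 to 12 month pilot: 435 to 870 people, or 17–33% of 2612. The documents do not support that as an estimate. The pilot is a feasibility exercise of unstated size, and not everyone would return, consent and be randomised. Setting the arm difference to zero in those people is also severe, since new or previously missed disease can still be found.

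**The accuracy study as a second source.** A reader might count its patients too. Study Settings does not say that their AI results reach the general clinics' record. They also carry an ophthalmologist's diagnosis, which would inform both arms. This route is too weak to rest the point on.

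**One person in both arms.** Because randomisation follows image upload, a reader might infer that a repeat photograph triggers a new draw. The Randomization section describes allocation per participant with a unique study ID, which largely answers this. Only a clarification remains.

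**Visibility of the report is not certain.** The text says reports can be integrated into the record, not that every pilot report is. Control physicians are also told to judge independently. That is an instruction, though; the document describes no means of keeping an old report out of view.

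**Bias is only towards the null.** Earlier exposure precedes randomisation and is balanced in expectation, so it does not favour AI. Enrolling previously screened people can be defended in a pragmatic trial. The loss of contrast remains.

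**Conclusion.** The point holds for the pilot route. As printed, the eligibility rule lets people with an unrandomised AI reading enter the randomised phase. Yearly follow-up can bring them back during recruitment, and nothing protects the control comparison from a report already on file. The consequence is conditional: the detection difference would be diluted in proportion to the overlap, which the document does not give. At an assumed 10% overlap with no arm difference in those people, the DR difference falls from 3.5 to about 3.2 points and power from about 89% to 82–84%. If the overlap is close to zero, so is the effect. The sample size calculation itself is sound. The change should be made before the first randomisation.

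**What to change.** **Preferred.** In Inclusion and Exclusion Criteria, exclude from the randomised phase anyone with a VeriSee DR or VeriSee AMD reading on record from the pilot. Have AIMIGS check the patient ID for a stored reading before it allocates. The cost is one criterion, one rule in the existing engine and a somewhat smaller recruitment pool. That loss grows with the overlap, so a large loss would arise only where the problem is large too.

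**Minimum, if pilot participants are to be kept.** Record earlier AI exposure at baseline, including any from the accuracy study, and prespecify a sensitivity analysis of detection rate and PPV excluding those participants. Exposure is fixed before allocation, so restricting the randomised set on it keeps the arms comparable. This costs one baseline field and one analysis, but leaves the dilution in the primary result.

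**Clarification.** Add one sentence to Randomization saying that later images of a randomised participant keep the original allocation.
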